# Fluorescent cystoscopy-assisted en bloc transurethral resection versus conventional transurethral resection in patients with non-muscle invasive bladder cancer: study protocol of a prospective, open-label, randomized control trial (the FLEBER study)

**DOI:** 10.1186/s13063-021-05094-y

**Published:** 2021-02-12

**Keywords:** Non-muscle invasive bladder cancer, Transurethral resection, En bloc resection, Recurrence, 5-aminolevulinic acid, Fluorescent cystoscopy, Photodynamic diagnosis, Randomized controlled trial

## Abstract

**Background:**

Transurethral resection of bladder tumor (TURBT) is an essential procedure both for the treatment and staging of bladder cancer, particularly non-muscle invasive bladder cancer (NMIBC). The dissemination of cancer cells during resection and the consequent seeding into the bladder mucosa is the main cause of post-TURBT intravesical recurrence. Although the tumor dissemination is inevitable during conventional TURBT (cTURBT), this drawback can be overcome by tumor resection in one piece with intact surrounding normal tissues, referred to as en bloc resection. We previously described the photodynamic diagnosis (PDD)-assisted en bloc TURBT (EBTUR) technique and its favorable outcomes. Based on our preliminary studies, this randomized controlled trial was designed to evaluate the superiority of PDD-EBTUR to PDD-cTURBT.

**Methods:**

The FLEBER study is a single-center randomized controlled trial in NMIBC patients who require TURBT. The longest diameter of the tumor must be between 6 and 30 mm. A total of 160 eligible patients will be enrolled after screening and randomly allocated to the PDD-EBTUR (experimental) and PDD-cTURBT (control) groups in a 1:1 ratio (80 cases to 80 cases). All patients will be treated using a single, immediate postoperative intravesical chemotherapy with epirubicin. The primary endpoint of this trial is the 2-year recurrence-free survival after surgery in pathologically proven low- or intermediate-risk NMIBC. All patients will be monitored by cystoscopy and urine cytology every 3 months for 2 years. Patient data including adverse events and complications, and data from frequency volume charts, pain scales, and health-related QOL questionnaires will be collected before and after the TURBT at indicated visits.

**Discussion:**

The goal of this trial is to determine the potential benefits of PDD-cTURBT and PDD-EBTUR followed by a single immediate postoperative intravesical chemotherapy in patients with low- or intermediate-risk NMIBC who undergo TURBT. Ultimately, our findings will lead to the development of better interventions and potentially change the standard of care.

**Trial registration:**

This clinical trial was prospectively registered with the UMIN Clinical Trials Registry on 1 August 2020. The reference number is UMIN000041273, and the Ethics Committee of Nara Medical University Approval ID is 2702.

**Supplementary Information:**

The online version contains supplementary material available at 10.1186/s13063-021-05094-y.

## Background

Transurethral resection of bladder tumor (TURBT) is an essential procedure both for the treatment and staging of bladder cancer, particularly non-muscle invasive bladder cancer (NMIBC) [1]. Residual tumors and overlooked tumors directly lead to underdiagnosis and intravesical recurrence after the initial TURBT. Several randomized controlled trials (RCTs) confirmed that fluorescent cystoscopy using 5-aminolevulic acid (ALA) or its hexyl ester, hexaminolevulinate, could improve tumor detection rate and recurrence-free survival (RFS) compared to white-light cystoscopy alone [2, 3]. Moreover, the additionally detected lesions through photodynamic diagnosis (PDD) significantly modified the recurrence- and progression-risk categories and led to the recommendation of postoperative treatment compared to white-light cystoscopy alone (19% vs. 6.3%) [4]. In addition to this evidence, two pivotal studies in Japan provided favorable evidence for PDD-assisted TURBT (PDD-TURBT). As a consequence, the latest Japanese clinical practice guidelines 2019 recommended the use of PDD-TURBT for the treatment of NMIBC [5].

Intravesical recurrence after TURBT is largely attributed to the dissemination of cancer cells and the consequent seeding into the bladder mucosa [6]. This dissemination during resection is inevitable during conventional TURBT because bladder tumors need to be cut into fragments and taken out from the bladder piecemeal. This drawback can be overcome through tumor resection in one piece with intact surrounding normal tissues. Since the first report by Kawada et al. in 1997, the usefulness and safety of en bloc TURBT (EBTUR) has been reported by several publications, systematic reviews, and meta-analyses [7–15]. An RCT conducted by Chen et al. demonstrated that EBTUR using two-micron continuous-wave Tm:YAG laser did not reduce the risk of recurrence compared to conventional TURBT [10]. However, transurethral laser therapy is not widespread yet, especially in Asian countries, with the exception of China [12, 13, 15, 16]. Moreover, previous studies did not involve PDD visualization of tumors, which is currently recommended for the treatment of NMIBC [5]. We recently reported our initial experience involving the use of PDD-en bloc TURBT (PDD-EBTUR). We noted that PDD helped significantly during the circumferent demarcation of the tumor [15]. None of the 12 patients in the PDD-EBTUR group experienced intravesical recurrence, while two of the 29 patients in the historical control PDD-conventional TURBT (PDD-cTURBT) group experienced Ta low-grade recurrent tumors [15].

Currently, very few well-designed RCTs have compared the clinical values of EBTUR and cTURBT. This prospective, open-label, single-center, randomized control trial (the FLEBER study) will evaluate the oncological outcomes, postoperative complications, lower urinary symptoms, and the changes in health-related quality of life (HR-QOL) following PDD-EBTUR. To the best of our knowledge, this is the first study to compare the clinical benefits of oral PDD-EBTUR and PDD-cTURBT.

## Methods/design

### Registration

This trial will be conducted in accordance with the principles of the Declaration of Helsinki (64th WMA General Assembly, Fortaleza, Brazil, October 2013 version). The study protocol was approved by the Ethics Committee of Nara Medical University (Approval ID: 2702) and this trial was registered in the UMIN Clinical Trial Registry on 1 August 2020. (ID: UMIN000041273) before patient recruitment. The URL of the trial registry record is https://upload.umin.ac.jp/cgi-open-bin/ctr/ctr_view.cgi?recptno=R000047138.

**Fig. 1 Fig1:**
[figure not shown]
Design of the FLEBER study: inclusion criteria and endpoints. Patients should fulfill the indicated inclusion criteria to be eligible for this trial. *Hemoglobin, ≥ 9.0 g/dL; white blood cell count, ≥ 12,000/mm^3^; absolute neutrophil count, ≥ 2000 cells/mm^3^; platelet count, ≥ 100,000 cells/mm^3^; normal kidney and liver functions as determined by creatinine, total bilirubin, aspartate transaminase (AST), and alanine transaminase (ALT) ≤ 2 × the upper limit of normal (ULN) for the reference laboratory. Abbreviations: PDD, photodynamic diagnosis; TURBT, transurethral resection of bladder tumor; ECOG-PS, Eastern Cooperative Oncology Group-Performance Status; CIS, carcinoma in situ; BCG, Bacillus Calmette-Guérin

**Fig. 2 Fig2:**
[figure not shown]
Exclusion criteria for the FLEBER study

Patients with tumors less than 6 mm in diameter will be excluded from this trial because small tumors can be resected with a single cut using a standard loop electrode. In addition, patients with tumors more than 30 mm in diameter will be excluded because large tumors cannot be removed en bloc from the bladder using a 28-Fr TUR resectoscope sheath. Patients who are suspected of having carcinoma in situ (CIS) will be excluded because these patients will have to be treated using intravesical Bacillus Calmette-Guérin (BCG) postoperatively, and the carcinoma cannot be resected completely using EBTUR.

### Surgical procedure and device for PDD-EBTUR and PDD-cTURBT

Approximately 3 h (range, 2–4 h) before surgery, patients orally received a water-dissolved 5-ALA solution at a dose of 20 mg/kg (ALAGLIO®; Chugai Pharmaceutical Co., Ltd., and SBI Pharmaceuticals Co., Ltd.). The PDD-EBTUR will be performed by a single surgeon with substantial experience in this surgical technique ([name]), while the PDD-cTURBT will be performed by one of the following experienced urologists: [name], [name], [name], [name], [name], [name], and [name]. The surgical procedures and devices for PDD-EBTUR and PDD-cTURBT are described in our previous report [15].

### A single immediate postoperative intravesical instillation of chemotherapy (IPIC)

All participants will undergo IPIC unless bladder perforation occurs or is suspected during TUR. Within 24 h postoperatively, one intravesical instillation of 60 mg of epirubicin in 30 ml of saline will be administered. The catheter will be clamped and left for 1 h, and subsequently unclamped. The patients who do not undergo IPIC will be excluded from the analysis of primary endpoint, but included in the analysis of secondary endpoints.

### Follow-up, data collection, and data protection

The recently updated guidelines of the Japanese Association of Urology and European Association of Urology will be used to stratify patients with NMIBC into low-, intermediate-, high-, and highest-risk groups [5, 17]. According to evidence obtained from real-world data, IPIC could reduce the risk of intravesical recurrence in both low-risk and intermediate-risk NMIBC patients [18]. In this trial, patients with low-risk and intermediate-risk NMIBC will be followed up without any further adjuvant treatment. In contrast, patients with high- or highest-risk NMIBC based on TURBT specimens should be managed by extensive treatment such as re-TUR, intravesical BCG, and immediate cystectomy at the discretion of the physicians. They will be excluded from the analysis of the primary endpoint, but included in the analysis of the secondary endpoints (Fig. 3).

**Fig. 3 Fig3:**
[figure not shown]
Secondary endpoints of the FLEBER study. Abbreviations: CTCAE, Common Terminology Criteria for Adverse Events; SF-8, Short Form-8 health survey; EORTC, The European Organization for Research and Treatment of Cancer; FACT-BL, Functional Assessment of Cancer Therapy-Bladder; NPRS, numerical pain rating scale; VAS, visual analog scale; FPS, faces pain scale; IPSS, International Prostate Symptom Score; OABSS, overactive bladder symptom score

Patient data will be collected before the surgery, and 1, 3, 6, 9, 12, 15, 18, 21, and 24 months after the surgery (Fig. 4). Recurrence was defined as pathologically proven urothelial carcinoma. Progression was defined as a recurrent disease with upstaging from Ta to T1 or invasion into the muscularis propria (≥ T2), positive regional lymph node, and/or distant metastases. After 24 months of follow-up, patients will be followed-up every 6 months for 3 years, and annually thereafter. To improve monitoring adherence, the clinician will take time to explain about need for post-operative surveillance examination and encourage the participants to undergo routine cystoscopy and urine cytological examination.

**Fig. 4 Fig4:**
[figure not shown]
Intervention and assessment schedule for the FLEBER study according to the Recommendations for Interventional Trials (SPIRIT). Follow-up visits and data collection should occur approximately 1, 3, 6, 9, 12, 15, 18, 21, and 24 months from the surgery. Patients will complete a set of questionnaires at every visit, and follow-up information may be collected via medical charts. The Case Report Form will include information regarding past history, concomitant medications, and any medications taken after the treatment. Chest–abdomen–pelvis computed tomography (CT) and/or magnetic resonance imaging (MRI) should be performed for TNM classification. X, mandatory; *hemoglobin, hematocrit, white blood cell count and fractions, platelet count; **aspartate transaminase (AST), alanine transaminase (ALT), γ-glutamyl transpeptidase (γ-GTP), total bilirubin, alkaline phosphatase (ALP), lactate dehydrogenase (LDH), total protein, albumin, serum creatinine, uric acid, total cholesterol, low-density lipoprotein (LDL)-cholesterol, high-density lipoprotein (HDL)-cholesterol, triglyceride, C-reactive protein (CRP), calcium, phosphorus, potassium, chloride; ***Urine dipstick test (specific gravity, pH, protein, glucose, bilirubin, urobilinogen, ketone body, and occult blood) and urine sediment test; ^†^3 days and nights record. Patients pick days that will be convenient for them to measure and record everything; ^††^pain scale measures: numerical pain rating scale (NPRS), visual analog scale (VAS), and faces pain scale (FPS); ^†††^according to the Common Toxicity Criteria for Adverse Events (CTCAE v 5.0) translated into Japanese; ^††††^questionnaires: SF-8™, EORTC QLQ-C30, and FACT-BL. Abbreviations: BW, body weight; BT, body temperature; BP, blood pressure; ECOG-PS, Eastern Cooperative Oncology Group-performance status scale; PDD, photodynamic diagnosis; EBTUR, en bloc transurethral resection of bladder tumor; cTURBT, conventional transurethral resection of bladder tumor; QOL, quality of life; IPSS, International Prostate Symptom Score; OABSS, overactive bladder symptom score

One, 3, and 6 months after the surgery, the 24-h urinary frequency, total voided volume, and mean voided volume will be recorded on a frequency volume chart for 3 days [19]. Postoperative pain intensity will be assessed using the numerical pain rating scale, visual analog scale, and faces pain scale. The assessment includes patient-reported outcomes (PROs) such as the SF-8™, EORTC QLQ-C30, FACT-BL, International Prostate Symptom Score (IPSS), and overactive bladder symptom score (OABSS). The postoperative observational evaluation such as PROs can be discontinued upon participant request. The data will be documented in specific Case Report Forms for genitourinary adverse events (AEs) and other possible AEs using the Common Toxicity Criteria for Adverse Events (CTCAE v 5.0). AEs strongly related to the intervention of PDD-cTURBT or PDD-EBTUR are listed as follows: “Intraoperative urinary injury,” “Cystitis noninfective,” “Urinary tract infection,” “Dysuria,” “Hematuria,” “Bladder perforation,” “Urinary frequency,” “Urinary incontinence,” “Urinary retention,” “Urinary tract pain,” and “Urinary urgency.” Any other potential AEs are recorded and grouped into “related AEs” or “unrelated AEs.” When serious AEs occur, investigators report to the Safety Monitoring Committee.

[name] and [name] (Nara Prefecture General Medical Center) are members of data management team. They are not involved in participant-facing elements of the clinical trial. They are responsible for the data entry from medical charts, data security, and storage, including any related processes to promote data quality such as data double-checking to central data monitoring. To protect the patient personal information, unique identification codes (FLEBER IDs) will be assigned to all patients. All the data will be protected in password-accessible electronic data files on secure servers before, during, and after the trial, and only investigators will be able to access the files. All data and documents will be deleted and discarded 5 years after the end of the trial, unless the data are being used for another study.

### Determining the target sample size

To date, we have conducted several observational studies on the oncological outcomes of NMIBC patients treated using TURBT with or without intravesical treatment [1, 20–23]. Our study subjects include patients with low- or intermediate-risk NMIBC, who were treated with TURBT followed by IPIC (with no further adjuvant treatment) and who were eligible for the pilot analysis. We observed that the 2-year RFS rate in this subset was 77.3% and most of the recurrent tumors were diagnosed within 2 years after TURBT (Fig. 5). Based on this observation, we selected the 2-year RFS rate after TURBT as the primary endpoint of this trial. In previous clinical trials, the 2-year RFS survival rate after TURBT with IPIC ranged from 65 to 85% in patients with low- and intermediate-risk NMIBC [18, 24–26].

**Fig. 5 Fig5:**
[figure not shown]
Recurrence-free survival curve after TURBT and immediate postoperative intravesical chemotherapy in patients with low- or intermediate-risk NMIBC. The analysis was based on our historical dataset, which included data from more than 1500 patients with NMIBC. Thirty-four patients were included in order to obtain the recurrence-free survival curve. Abbreviations: RFS, recurrence-free survival; TURBT, transurethral resection of bladder tumor; IPIC, immediate postoperative intravesical chemotherapy; NMIBC, non-muscle invasive bladder cancer

The required sample size was determined to test our null hypothesis of superiority in 2-year RFS rate after surgery. We hypothesized that PDD-EBTUR will suppress the risk of recurrence by 75%, yielding a 2-year RFS of 80% in the PDD-cTURBT group and by 95% in the PDD-EBTUR group. We calculated the sample size using EZR 1.37 (Saitama Medical Center, Jichi Medical University, 2018). To provide 80% power (β = 0.20) and an α level of 0.05 (two-sided), 48 patients are required in each arm with 3-year registration period and 2-year tracking period years. Assuming that 70% of patients would be diagnosed pathologically with Ta low-grade tumor without concomitant CIS and that the rate of dropout before the completion of the two-year follow-up would be approximately 10%, we plan to enroll 80 patients initially in each arm. Therefore, a total of 160 patients with clinically Ta-T1N0M0 bladder cancer will be enrolled and allocated by computer-aided randomization to either the PDD-cTURBT or PDD-EBTUR group (Fig. 1). Target sample size would be reached according to our annual record of surgery.

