### Statistical analysis

The full analysis set (FAS) population will be analyzed for both the primary endpoint (2-year RFS rate) and survival outcomes (Fig. 3; RFS after 2 years, progression-free survival, progression-free rate, upper urinary tract cancer-free survival, metastasis-free survival, cancer-specific survival, and overall survival), and the per protocol set (PPS) population will be analyzed for the other secondary endpoints. A two-sided *P* value of less than 0.05 will be considered to be statistically significant.

To compare the PDD-cTURBT and PDD-EBTUR groups, descriptive statistical analysis will be performed for all study variables. To assess the prognostic impact of the surgical procedure and clinicopathological parameters, event-free survivals will be estimated using the computing risks model; this model considers patients who die of other causes (competing events) before recurrence or progression. The Gray test and Fine-Gray subdistribution hazard regression will be applied to the primary endpoint and the survival outcomes at the secondary endpoints to compare the groups and to calculate the hazard ratio. In addition, a sensitivity analysis of the primary endpoint will be performed using the log-rank test and Cox proportional hazard regression analysis. The amount of change in other post-operative observations over time will be analyzed using the repeated measures analysis of variance (ANOVA), Wilcoxon signed-rank sum test, or Mann-Whitney *U* test. For analyses of cross-sectional measures for continuous and categorical variables, the Mann-Whitney *U* test and Fisher’s exact test, respectively, will be used. A subgroup analysis will be performed to examine whether effects of the intervention differ between subgroups according to the characteristics of patients.

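### 48 per arm gives 80% power only if recurrences over 2 to 5 years of follow-up count; for the stated 2-year RFS endpoint, power is about 60–68%

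*Protocol article*

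**What the plan says.** The Abstract (Methods) defines the endpoint: "The primary endpoint of this trial is the 2-year recurrence-free survival after surgery in pathologically proven low- or intermediate-risk NMIBC". The section on determining the target sample size says that the calculation tests the 2-year RFS rate, with the hypothesised effect "yielding a 2-year RFS of 80% in the PDD-cTURBT group and by 95% in the PDD-EBTUR group". The error rates are "To provide 80% power (β = 0.20") and "an α level of 0.05 (two-sided"), and the result is "48 patients are required in each arm with 3-year registration period and 2-year tracking period years". It then assumes that 70% of patients will be pathologically eligible and about 10% will drop out, and arrives at 80 enrolled per arm.

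The Statistical analysis section again names the 2-year RFS rate as primary. It lists later recurrence-free survival among the other survival outcomes: "RFS after 2 years, progression-free survival, progression-free rate". The Gray test and Fine-Gray regression are assigned to the primary endpoint, with log-rank and Cox as sensitivity analyses. No time horizon for these tests is stated. The interim analysis section describes the trial as having 2 years of follow-up.

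**The concern.** An accrual period and a further follow-up period are inputs to a survival-curve calculation in which the first patient is observed for 5 years and the last for 2. An endpoint fixed at 2 years gains nothing from observation beyond month 24, so the accrual period should not reduce the required number. If the 48 depends on recurrences after month 24, the 80% power belongs to a different comparison from the one the section says it sized.

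At stake is how a null result is read. A trial reported as having 80% power would be taken as fairly strong evidence against the hypothesised effect. If the chance of missing that effect is nearer 32–40% than 20%, that reading is too strong.

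**Working it through.** **Inputs (sample size section; 1:1 allocation from the Abstract).** 2-year RFS 80% and 95%; two-sided alpha 0.05; power 80%; accrual 3 years; further follow-up 2 years.

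**Hazards.** With exponential survival, λ = −ln(S)/2. This gives λ1 = 0.1116 and λ2 = 0.0256 per year, hazard ratio 0.230, difference 0.0859, mean λ̄ = 0.0686.

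**Formula (hazard-difference, Lachin type).** With P(λ) the probability of an observed event and φ(λ) = λ²/P(λ),

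n per arm = [1.960·√(2φ(λ̄)) + 0.842·√(φ(λ1)+φ(λ2))]² / (λ1−λ2)².

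**Step 1: reproduce the 48.** With uniform accrual over 3 years and 2 more years, P(λ) = 1 − [exp(−2λ) − exp(−5λ)]/(3λ).
- Event probabilities are 0.320 and 0.086 (0.212 at λ̄).
- The two square roots are 0.2107 and 0.2158.
- n = (0.4130 + 0.1817)²/0.0859² = 47.9, so 48.
- Expected events are 48 × (0.320 + 0.086) = 19.5.

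**Step 2: count to 2 years only.** P(λ) = 1 − exp(−2λ).
- Event probabilities are 0.20 and 0.05 (0.128 at λ̄).
- The two square roots are 0.2710 and 0.2746.
- n = (0.5311 + 0.2312)²/0.0859² = 78.7, so 79.
- Expected events at 48 per arm are 48 × 0.25 = 12, so 7.5 of the 19.5 (38%) are lost.

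**Step 3: other methods at a fixed 2 years, two-sided.** Required per arm: two proportions 76 (88 with continuity correction), Lakatos type 77, Freedman 81, Schoenfeld 59. Simulated log-rank power (20,000 runs) reaches 80% at about 70 per arm. None gives 48. A one-sided Schoenfeld calculation gives 46, but the protocol states a two-sided test.

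**Step 4: power of the plan as it stands.** Enrolment of 80 per arm gives 80 × 0.7 × 0.9 = 50.4 evaluable, or 80 × 0.7 = 56 if dropouts stay in the analysis and are censored.

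| Per arm, events to 2 years | Freedman | Hazard difference | Two proportions | Simulated log-rank |
|---|---|---|---|---|
| 48 | 58% | 59% | 61% | 63–64% |
| 50 | 60% | 61% | 62% | 65–66% |
| 56, 10% censored over 2 years | – | – | – | 67–68% |

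Schoenfeld gives 72% at 48 and 74% at 50. It is optimistic at so extreme a hazard ratio: in the 2-to-5-year setting it gives 90% where simulation gives 85%. Fisher's exact test gives 48% at 48 per arm.

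**Step 5: enrolment needed for 80% at 2 years.** With 0.7 × 0.9 = 0.63, 76 to 81 evaluable means 76/0.63 ≈ 121 to 81/0.63 ≈ 129 enrolled per arm. Taking the simulation's 70, it is 70/0.63 ≈ 111. The plan has 80.

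**Step 6: if all follow-up is used.** The hazard after year 2 is not given, so it is an assumption here. Simulated log-rank power at 50 per arm, with the late hazard at 0.10, 0.25, 0.50, 0.75 and 1.0 times the early one, is about 69%, 72%, 78%, 82–83% and 86%.

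**The case against.** The strongest reply is that the primary test may not be cut at 2 years. The article sets no horizon for the Gray test, follow-up visits continue after month 24, and recruitment to July 2023 with data collection to July 2025 matches the 3 + 2 years in the calculation. On that reading sizing and analysis agree, and the stated power is met under a constant hazard. This stands as a possibility, so the shortfall is conditional on counting events to 2 years. But that condition is what the article says: the endpoint and the sized hypothesis are both the 2-year RFS rate, and later RFS is listed apart from it.

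A reader might also infer that the article contradicts its own constant hazard, because it reports that "most of the recurrent tumors were diagnosed within 2 years after TURBT". It does not. Under the constant-hazard calculation, 12 of 19.5 events (62%) already fall within 2 years, which is most of them. The historical curve rests on 34 patients and its figure is not shown. The documents do not describe a falling hazard, and they do not support a single figure such as 70% for a whole-curve test.

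Nor is 48 an arithmetic slip. It is correct for its inputs.

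**Conclusion.** The point holds as a mismatch between the endpoint and its sample size. The 80% power belongs to a comparison that counts recurrences over 2 to 5 years at a constant hazard. For the 2-year endpoint as stated, the planned enrolment gives about 60–68% power for 80% versus 95%. The low end treats dropouts as contributing nothing; the high end keeps 56 per arm with 10% censored.

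This assumes exponential recurrence within 2 years, the protocol's own 70% and 10%, and too few deaths before recurrence for the Gray test to behave much differently from log-rank. The exact value depends on the method, but none of those tried reaches 80% at 48 or 50 per arm with events counted to 2 years.

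**What to change.** Keep 160 patients. In the sample size section, state that about 50 evaluable patients per arm (56 with dropouts censored) give roughly 60–68% power for 80% versus 95% at 2 years. Add that the 80% figure applies only if recurrences over the full 2 to 5 years are counted at a constant hazard. State the time horizon of the primary Gray test.

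If the sponsor intends that test to use all follow-up, the primary endpoint wording has to say so, its overlap with the separate later-RFS outcome has to be resolved, and power should be given as a range (about 69–86% at 50 per arm) with the late-hazard assumption named. That redefines the primary endpoint of a recruiting trial, so it is a trade-off and more than a wording change.

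Restating the power costs only text in the protocol and in any other document that repeats the figure. It needs no extra patients or visits. The downside is a less favourable stated power.
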